### Ethical considerations

Patients will be identified in all study documents and questionnaires by a unique study identification number that will be used to link multiple study records for each participant. No personally identifiable information on any participant will be collected or removed from the participating centres in order to preserve patient confidentiality. Patients will provide written informed consent according to the Research Ethics Committee (REC)-approved protocol and consent materials. Only patients providing written informed consent will be included in the study and no data collection on an individual will take place until their written informed consent has been obtained. Participants will have the right to withdraw their consent at any time, without giving a reason and without prejudice to their normal care. NHS management approval for local conduct of the study and the sharing of pseudonymised patient data will be sought via the Research and Development department in each participating centre.

### Statistical methods

#### Study sample size

Study endpoints will be described for the overall patient population and in patients stratified by anticoagulant treatment received; however, no formal comparisons between groups will be made. Therefore the required sample size was estimated based on precision (95% confidence limits) rather than statistical power. For Group 1 a sample size of 300 patients is considered sufficient to reliably describe the demographics and clinical characteristics of the study population. Based on feasibility interviews with a small sample of UK clinicians it is anticipated that approximately 80% of patients in Group 1 are likely to be prescribed a DOAC for secondary prevention of stroke. Therefore, a sample size of 150 patients in Group 2 distributed evenly between patients initiated on apixaban, edoxaban and rivaroxaban is considered feasible. A sample size of 50 patients treated with each of the anti-FXa DOACs is considered sufficient to give reliable estimates of patient adherence based on scores from a previously published study of DOAC adherence [24]. For a sample of 50 patients with a mean adherence score of 7.2 and a standard deviation of 1.2, the lower and upper confidence limits are expected to be between 6.9 and 7.5, indicating the sample size is sufficient to provide a reliable estimate of mean adherence score.

### Data analysis

Statistical analyses, including any data preparation prior to analysis, will be carried out using Stata v14 (StataCorp LLC) and Microsoft Excel (2010). Data from all centres will be pooled for analysis. Study endpoints will be presented as descriptive statistics of central tendency (median; arithmetic mean or geometric mean) and dispersion (interquartile range [IQR] and/or range; standard deviation [SD] and/or 95% confidence intervals [95% CI]) and/or frequencies and percentages, as appropriate for the type and distribution of the variables.

Total scores for the validated patient-reported questionnaires will be derived in accordance with published scoring algorithms for each measure [17, 18, 25]_._ Analyses will be conducted using only the results of those patients with data available.

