### Prospective patient survey

Patient-reported outcome data will be collected prospectively from patients in Group 2 via questionnaires administered at baseline (initiation of anti-FXa DOAC treatment + 1 month), and at 3 months (− 1 week/+ 1 month) and 6 months (− 1 week/+ 1 month) after initiation of anti-FXa DOAC treatment for secondary prevention of stroke. These time-points were chosen in order to allow an adequate amount of time between assessment points for DOAC treatment to take effect. Questionnaires will be administered face-to-face if patients are attending clinic at the relevant time point; they will be reminded of the study requirements and will be given the opportunity to decide whether or not they would still like to take part, prior to the questionnaire being administered. Otherwise questionnaires will be administered via telephone, which is a methodology for administration of patient questionnaires that has been used in prior studies, including a study relating to edoxaban treatment [16]. Where questionnaires are administered by telephone, the questionnaires will be posted to patients by members of their direct care team at the relevant time points to give patients an opportunity to contemplate their responses and complete the questionnaires in advance. Patients will be contacted by telephone to advise them that the questionnaire has been posted, to remind them of the study requirements and to ensure that they are still willing to participate in the study. A member of the direct care team or an external researcher will contact patients at an agreed date and time to collect their responses via telephone. The questions will be read to patients as written on the paper version and patients’ responses will be entered directly into the eCRF.

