Patient reported outcome measures include the Morisky Medication Adherence Scale (MMAS-8) questionnaire [17] and the Treatment Satisfaction Questionnaire for Medication (TSQM) questionnaire [18]. The MMAS-8 is a short, eight-item measure of treatment adherence that has previously been used to assess adherence to DOAC treatment in patients with venous thromboembolism [19]. The MMAS has been used widely in different diseases, populations and countries and has been administered face-to-face or via telephone [20–22]. The MMAS-8 is quicker to complete and has a higher degree of concordance with more objective measures of treatment (such as pharmacy fill data or electronic monitoring devices) than many other self-report measures [20]. In order to gain additional insight into recent levels of treatment adherence, patients will also be asked to report whether, how and how often they had taken their current anti-FXa DOAC treatment in the past seven days using a bespoke questionnaire. The TSQM is a widely validated general measure of treatment satisfaction which has been used for a variety of treatments and disease areas, including for measuring levels of patient satisfaction with anticoagulation treatment [23], and has been administered face-to face or via telephone [22]. The bespoke questionnaire will be administered to gain an understanding of the general experiences of patients with regard to other aspects of their care, such as communication, education about anti-FXa DOAC treatment and overall hospital experience.

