### Subgroup and sensitivity analyses

All endpoints evaluated in Group 2 will be stratified according to the anti-FXa DOAC first prescribed (apixaban, edoxaban, rivaroxaban). Patient-reported outcomes will also be analysed separately for patients remaining on first anti-FXa DOAC treatment and those switching DOAC treatment during the post-DOAC observation period, in order to explore the relationship between patient-related factors and decisions to switch treatments. No sensitivity analyses are planned.

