### Limitations of the research methods

Based on feasibility assessments it is expected that all relevant data to evaluate the CHA_2_DS_2_-VASc risk score will be available for all patients. However, it is possible that some or all of the required components needed to calculate the CHA_2_DS_2_-VASc score will be unavailable for some patients, which may introduce bias in terms of a reduction in the sample size and may lead to underestimation of stroke risk. The exclusion of patients with persisting cognitive or emotive deficit at the time of consent may lead to an underestimation of hospital resource use; patient-reported outcomes may also not be representative of the wider patient population. In addition, primary care data following discharge home from hospital after stroke and/or data relating to patient management prior to stroke may also not be available for all patients, which may affect the related endpoints. This is a descriptive study and no comparative analyses or analyses to control for confounding factors will be carried out. As such, no inferences about causal relationships between different DOACs and study endpoints and how treatments compare to each other will be made. For patient-reported measures, the data will rely on the completeness of the answers provided by participants, which will not be queried or otherwise followed up to clarify inconsistencies or omissions. The importance of providing honest and complete responses at each time point will be emphasised to patients; data may however be subject to patient recall and reporting bias. Patient-reported data based on recall (for example, for adherence to medication) may also be subject to recall bias and/or reporting bias.

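### Three- and six-month patient-reported scores rest on whoever responds, with no sensitivity analysis, so later adherence means may be overstated if non-responders adhere less

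*Protocol article*

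**What the plan says.** All points are in the protocol article.

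- **Analysis set (Data analysis).** Analyses are to be run "using only the results of those patients with data available". No imputation or model for missing scores is described.
- **Sensitivity analyses (Subgroup and sensitivity analyses).** "No sensitivity analyses are planned".
- **Timing (Prospective patient survey).** Questionnaires are given at baseline and "at 3 months (− 1 week/+ 1 month) and 6 months (− 1 week/+ 1 month) after initiation of anti-FXa DOAC treatment".
- **Leaving the survey (same section).** Patients seen in clinic "will be given the opportunity to decide whether or not they would still like to take part, prior to the questionnaire being administered". Those surveyed by telephone are also asked whether they are still willing.
- **Incomplete answers (Limitations of the research methods).** Patient-reported data depend on the completeness of the answers, "which will not be queried or otherwise followed up to clarify inconsistencies or omissions".
- **Treatment course (Subgroup and sensitivity analyses).** Patient-reported outcomes are "analysed separately for patients remaining on first anti-FXa DOAC treatment and those switching DOAC treatment during the post-DOAC observation period". No stratum is named for patients who stop without switching.
- **Bespoke adherence item (Study endpoints and variables).** It asks whether, how and "how often they had taken their current anti-FXa DOAC treatment in the past seven days".
- **Precision (Study sample size).** With 50 patients per drug, a mean adherence score of 7.2 and an SD of 1.2, the limits are given as 6.9 to 7.5. No allowance for non-response is stated.

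**The concern.** Describing patient-reported adherence and satisfaction is among the secondary objectives, and the adherence score is the only endpoint with a precision calculation. The scores are repeated over six months in a survey that patients can leave at each contact. The reason for leaving may be tied to what is being measured: a patient who has disengaged from treatment is plausibly less likely to answer questions about taking it.

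Under an available-case rule, each visit then describes a different set of patients. If those lost adhere less, the 3- and 6-month means are too high for the group that started treatment. A reader comparing visits could take a change in who answered for a change in adherence. The confidence interval widens as numbers fall, but it does not show this bias.

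The limitations section covers incomplete answers, recall and reporting bias, and the exclusion of patients with cognitive or emotive deficit. It does not mention selective loss of respondents over time, and with sensitivity analyses ruled out nothing planned would reveal it.

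**Working it through.** **1. Reproduce the plan's figure.** Inputs from Study sample size: n = 50, mean 7.2, SD 1.2, 95% limits.

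- Normal: 1.96 × 1.2/√50 = 0.333, giving 6.87 to 7.53.
- t with 49 degrees of freedom: half-width 0.341, giving 6.86 to 7.54.

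Both round to the stated 6.9 to 7.5. The figure is correct, provided all 50 patients per drug give a score.

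**2. Precision with fewer responders** (t-based, same SD):

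| Responders | Half-width |
|---|---|
| 50 | 0.34 |
| 45 | 0.36 |
| 40 | 0.38 |
| 35 | 0.41 |

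The loss of precision is modest.

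**3. Bias of the available-case mean.** Let d be the share without a score at a visit, R the responders' mean and N the mean the non-responders would have had. The full-group mean is (1 − d)R + dN, so

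bias = R − [(1 − d)R + dN] = d × (R − N).

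The article gives neither d nor R − N. Both are assumptions here:

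| Share missing | Gap 0 | Gap 0.5 | Gap 1.0 | Gap 1.5 |
|---|---|---|---|---|
| 10% | 0 | 0.05 | 0.10 | 0.15 |
| 20% | 0 | 0.10 | 0.20 | 0.30 |
| 30% | 0 | 0.15 | 0.30 | 0.45 |

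A reversed gap gives a negative bias. For the bias to equal the half-width of 0.341, the gap would have to be 0.341/d: 3.4 points at 10% missing, 1.7 at 20% and 1.1 at 30%. Within the table, only 30% missing with a gap of 1.5 exceeds it.

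**4. Effect on reading the visits side by side.** Suppose everyone answers at baseline (mean 7.2) and the true 6-month mean is 7.0. The observed 6-month mean is 7.0 + d × gap:

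- 10% missing, gap 0.5: 7.05, so the fall is still visible.
- 20% missing, gap 1.0: 7.20, so the fall is hidden.
- 30% missing, gap 1.0: 7.30, an apparent rise.

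A true fall of 0.2 is fully hidden once d × gap reaches 0.2.

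**5. Scope.** These figures concern the adherence score used for the sample size, read here as the MMAS-8. The same rule governs the TSQM, but the article gives no SD or expected value for it, so no size is offered for satisfaction.

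**The case against.** The strongest case against has five parts.

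- **Patients who stop do not vanish.** A reader might infer that they drop out of the results altogether. The documents do not support this. Discontinuation, its timing and its reasons are separate Group 2 endpoints (Study endpoints and variables), prescribing details come from medical records, and switchers have their own stratum. Nor does any section say that stopping ends the survey: questionnaires are timed from initiation. The reference to the current DOAC belongs to the bespoke seven-day item, not to the MMAS-8 or TSQM. All of this stands. What remains is narrower: it is unstated how patients who stop without switching are handled in the scores, and a separate discontinuation count does not correct a 6-month mean.
- **Direction and size are unknown.** This stands, so the point must be conditional.
- **Loss may be small.** Patients unwilling or unable to complete questionnaires are not eligible for Group 2, and telephone collection comes with posted forms, an advance call and an agreed time. These steps could keep loss near or below the low end of the assumed range, but they do not remove the opt-out at each contact.
- **The study is descriptive.** No test of change over time is planned, so any trend is one the reader draws. True, but a descriptive mean can still be biased, and three visits side by side invite that reading.
- **Responder counts usually belong in an analysis plan.** Their absence from an article is no fault. The available-case rule and the exclusion of sensitivity analyses, however, are choices the article states.

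**Conclusion.** The concern holds in conditional form. The article fixes an available-case rule for repeated patient-reported scores, rules out any check on it, and does not list selective loss of respondents as a limitation. If non-responders or stoppers adhere less, the 3- and 6-month MMAS-8 means may be overstated by 0.05 to 0.45 points, ranging from negligible to larger than the half-width of about 0.34. That range rests on assumed loss of 10% to 30% and assumed gaps of 0.5 to 1.5 points. With no gap there is no bias.

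A reader might go further and infer that adherence will appear to hold or rise, or that satisfaction will be overstated too. The documents do not support either as a prediction: they contain no loss rate, no score gap and no figures for the TSQM. The primary endpoint is not touched by this point. The change is worth making because it is cheap and would show whether differences between visits reflect who remained.

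**What to change.** Keep the available-case table as the main presentation and add:

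1. The number responding at each visit, and within-patient change from baseline in patients with both assessments.
2. Baseline scores of patients with and without 3-month data, and likewise for 6 months.
3. A separate row for patients recorded as having stopped without replacement, with a statement of whether they are still surveyed.
4. One sensitivity analysis that shifts missing scores downward over a stated range, for example 0 to 1.5 points below responders, reporting the mean at each step.

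Do not count every non-responder as non-adherent. That is an extreme assumption, does not define a value for a mean score, and mixes stopping treatment with taking it irregularly.

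Amend the statement in Subgroup and sensitivity analyses so that it no longer covers these endpoints, and add selective loss of respondents over time to Limitations of the research methods.

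**Cost.** A few extra descriptive rows and one simple analysis, from scores and discontinuation records already collected and linked by study number. The possible downside is a less favourable adherence figure alongside the main one.

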### Subgroup and sensitivity analyses

All endpoints evaluated in Group 2 will be stratified according to the anti-FXa DOAC first prescribed (apixaban, edoxaban, rivaroxaban). Patient-reported outcomes will also be analysed separately for patients remaining on first anti-FXa DOAC treatment and those switching DOAC treatment during the post-DOAC observation period, in order to explore the relationship between patient-related factors and decisions to switch treatments. No sensitivity analyses are planned.

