### Study endpoints and variables

The primary endpoint of the study is the CHA_2_DS_2_-VASc Risk Score (scores range from 0 to 9) prior to initiation of anticoagulation for patients included in Group 1. Secondary endpoints to be evaluated in patients in Group 1 include patient demographics (including age, sex, body mass index [BMI], smoking status, alcohol use, ethnicity) and clinical characteristics (including time from AF diagnosis until stroke, recorded stroke severity, location of presentation with stroke [e.g. Emergency Department (ED), inpatient, outpatient, GP], and key clinical and laboratory evaluations at the time of stroke (including renal function, liver function and blood parameters), relevant medical history (including history of congestive heart failure, hypertension, diabetes mellitus, vascular disease [including myocardial infarction, aortic plaque, peripheral vascular disease], renal disease, hepatic disease), anticoagulant therapy initiated for secondary prevention of stroke, and relevant concomitant medication at the time of stroke and prescribed in the one month period after stroke. Secondary endpoints to be evaluated in patients in Group 2 include: the time between index event and date of anti-FXa DOAC initiation; anti-FXa DOACs and other anticoagulants prescribed during the post-DOAC observation period (including dose, and dosing frequency and reason for choice of first DOAC treatment, changes in dose and reasons for dose changes, DOAC discontinuation, time from initiation to discontinuation of first DOAC and reason(s) for discontinuation, anticoagulant treatments subsequently prescribed and reason(s) for choice/discontinuation); relevant medications newly prescribed in the post-DOAC observation period; clinical assessments (types and results of clinical assessments); hospital resource use (number, type [outpatient, inpatient, ED, other; planned or unplanned], setting [face-to-face, telephone, other], reason for hospital visits/consultations, length of stay for inpatient admissions, time to first follow-up visit from date of DOAC initiation) during the post-DOAC observation period.

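### The analysis meant to explore decisions to switch DOAC is not limited to scores given before the switch, and its two groups leave out patients who stop or move to a non-DOAC

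*Protocol article*

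**What the plan says.** Three parts of the protocol article bear on this.

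- **Subgroup and sensitivity analyses** sets the strata: "All endpoints evaluated in Group 2 will be stratified according to the anti-FXa DOAC first prescribed (apixaban, edoxaban, rivaroxaban"). It then says that patient-reported outcomes will also be "analysed separately for patients remaining on first anti-FXa DOAC treatment and those switching DOAC treatment during the post-DOAC observation period", and gives the purpose: "in order to explore the relationship between patient-related factors and decisions to switch treatments". The section closes with "No sensitivity analyses are planned".
- **Prospective patient survey** counts the follow-up questionnaires from the start of the first DOAC: "at 3 months (− 1 week/+ 1 month) and 6 months (− 1 week/+ 1 month) after initiation of anti-FXa DOAC treatment". A baseline questionnaire is due within one month of initiation.
- **Study endpoints and variables** says that the bespoke items ask "how often they had taken their current anti-FXa DOAC treatment in the past seven days using a bespoke questionnaire". The same section lists, from the medical records, "time from initiation to discontinuation of first DOAC and reason(s) for discontinuation, anticoagulant treatments subsequently prescribed".

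**The concern.** The switch analysis has a stated question: how patient-related factors relate to the decision to switch. Only what the patient reported before the decision can inform that. The text sorts patients by an event during follow-up and puts no matching limit on which of their questionnaires count. The reference to the post-DOAC observation period dates the switch, not the scores. Followed as written, the analysis lets a switcher's scores on the second drug in beside those on the first. A difference from stayers could then reflect a reason for switching or a result of it.

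The two named groups also do not cover everyone. The article expects discontinuation and later anticoagulants of other kinds. A patient who stops has neither remained nor switched. A patient who moves to a non-DOAC has not, on a plain reading, switched DOAC. These patients may be among the most informative about dissatisfaction.

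A lesser matter concerns the first-drug strata. The seven-day items ask about the current DOAC, so after a switch the answer describes the second drug and is tabulated under the first.

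These are secondary endpoints. At stake is whether the switch analysis answers its own question, and whether the adherence tables are read correctly.

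**Working it through.** **1. Which scores can bear on the decision.** Questionnaire times come from Prospective patient survey. A switch can fall in four places:

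| Switch occurs | Last score before the switch | Scores on a later drug |
|---|---|---|
| Before the baseline questionnaire is completed (it may be up to one month after initiation) | none | baseline, 3 and 6 months |
| Between baseline and 3 months | baseline | 3 and 6 months |
| Between 3 and 6 months | 3 months | 6 months |
| After the 6-month questionnaire | 6 months | none |

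Only the middle column is relevant to the stated purpose. Tabulating by visit does not do this by itself. The switchers' 3-month row, for example, would mix early switchers answering on the second drug with later switchers still on the first.

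**2. Whether the data allow the restriction.** Time to discontinuation of the first DOAC, its reasons and subsequent anticoagulants are collected. Questionnaires have defined windows, so their completion dates should be known. A pre-switch analysis is therefore possible for every row except the first.

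**3. The plan's own precision figure.** Inputs from Study sample size: n = 50 per DOAC, mean adherence score 7.2, SD 1.2, 95% limits.

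- Normal: 7.2 ± 1.96 × 1.2/√50 = 7.2 ± 0.333, or 6.87 to 7.53.
- t with 49 df: 7.2 ± 0.341, or 6.86 to 7.54.

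Both round to the stated 6.9 to 7.5, so the planned half-width of about 0.33 is reproduced.

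**4. Effect of post-switch scores on a first-drug stratum.** If a share s of the stratum has switched by a questionnaire, and switchers' scores then differ by d from what they would be on the first drug, the mean moves by s × d. The documents give neither value, so both are assumed. The last column is the half-width 1.96 × 1.2/√n when only the patients still on the first drug are kept.

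| s | Switchers of 50 | Shift, d = 0.5 | Shift, d = 1.2 (1 SD) | n still on first drug | Half-width |
|---|---|---|---|---|---|
| 6% | 3 | 0.03 | 0.07 | 47 | 0.34 |
| 10% | 5 | 0.05 | 0.12 | 45 | 0.35 |
| 20% | 10 | 0.10 | 0.24 | 40 | 0.37 |
| 30% | 15 | 0.15 | 0.36 | 35 | 0.40 |

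The shift reaches the planned half-width only in the bottom row with a full SD of difference.

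**5. Precision of the switch analysis.** With the same assumed shares across all 150 patients in Group 2, there are 9, 15, 30 or 45 switchers. With SD 1.2, the t half-widths for their mean score are 0.92, 0.66, 0.45 and 0.36. These are best cases, because a switcher with no pre-switch questionnaire drops out.

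**The case against.** The strongest reply has four parts.

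- **The text is silent on which scores are used.** A reader might infer that switchers will be analysed on scores pooled over the whole period, and even that this could make switchers look more satisfied than stayers. The article does not support that: it plans no pooling across visits and does not say which questionnaires count. A reversal can be produced only by averaging visits under invented scores. This part of the reply stands. What remains is that the purpose is fixed in the article and the restriction which that purpose needs is not.
- **A SAP may settle it.** Choosing questionnaires and table rows is often SAP detail, and the SAP is not shown. That lowers the weight of the point. It does not remove it, because the two groups and the aim are set here and do not fit each other as written.
- **Grouping by first drug is legitimate.** Group 2 is recruited by the DOAC initiated, the strata are named as first prescribed, and the article rules out inferences about how the DOACs compare. This stands. A reader might infer that these tables report the wrong drug. They do not; they describe patients by initial treatment. Moreover, only the seven-day items are documented as being about the current DOAC. The article states no reference drug for MMAS-8 or TSQM.
- **Patients remaining on the first drug are already shown separately.** This helps in part. But that group is defined over the whole follow-up, so a patient who switches at month 5 is not in it, although the 3-month score was given on the first drug.

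**Conclusion.** The point holds for the switch analysis. Its stated aim needs scores from before the switch, the text does not restrict it to them, and patients who stop or change to a non-DOAC have no clear place. It would be too strong to say that the study cannot address why patients switch: the records and the separate visits allow a pre-switch analysis wherever a questionnaire came before the switch.

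For the first-drug strata the point is one of labelling and a supplementary table, not of error. Under the assumed shares and differences the shift is 0.03 to 0.36 adherence points against a half-width of 0.33: small if few switch, and comparable only at about 30% switching with a difference of one SD. The true size cannot be given, because the documents state no switch rate.

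**What to change.** 1. For the switch question, use the last questionnaire completed before the switch or stop date, and set it against stayers' scores at the same visit.
2. Show four rows: stayed on first DOAC, switched DOAC, changed to another anticoagulant, stopped. Report how many patients in the last three had no questionnaire before the change.
3. Keep the strata by first-prescribed DOAC and label them as initial drug. Beside them, show the 3- and 6-month patient-reported scores in each stratum for patients still on that drug at the questionnaire.

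The cost is wording and a few extra tables; the treatment data are already collected. The switch analysis will be small, and some switchers will drop out of it for want of an earlier score, so it should be presented as exploratory with its counts. The on-drug tables lose a little precision: for example, the half-width goes from 0.33 to 0.35 if 5 of 50 have switched.
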